## Abstract

**Background:**

N-methyl-D-aspartate receptor antagonists are potential therapies for neuropathic pain, and memantine has a good tolerance profile. A preclinical study recently reported that presurgery memantine may prevent neuropathic pain development and cognition dysfunction. Considering the high prevalence of breast cancer and of post-mastectomy neuropathic pain, a clinical trial is carried out to evaluate if memantine may prevent neuropathic pain development and maintain cognitive function and quality of life in cancer patients.

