### Objectives

The primary objective of this study is to evaluate if memantine administered before and after mastectomy may prevent pain development at 3 months post-mastectomy when compared to the placebo group. The endpoint at 3 months was chosen because chronic pain is usually defined as pain lasting longer than 2 to 3 months [17, 18], and 6 months was included as a secondary endpoint.

The secondary objectives are to estimate at 3 and 6 months post-mastectomy the pain intensity, the analgesic concomitant medications, the impact of treatment (memantine/placebo) on cognitive function, quality of life, sleep, anxiety and depression, the impact of cancer chemotherapy-induced pain and cognitive impairment and the prevalence of phantom breast experience.

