### Definition of endpoints and outcome measures

#### Primary endpoint

The primary endpoint is the pain intensity evaluation by numerical scale in memantine and placebo groups at 3 months post-mastectomy. The scale ranges from 0 (no pain) to 10 (maximal tolerable pain).

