#### Secondary endpoints

Secondary endpoints are the evaluation of pain at the screening visit, at 2 weeks, 3 months and 6 months after mastectomy (numerical scale, Brief pain Inventory, McGill pain questionnaire), neuropathic pain (Neuropathic Pain in 4 questions, Neuropathic Pain Symptom Inventory), cognition (Trail Making Test, Digit Symbol Substitution Test), sleep (Leeds sleep questionnaire), quality of life (Short-Form-36), and anxiety and depression (Hospital Anxiety and Depression scale). The summary of the different evaluations for a patient is reported in Table 1.

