### Statistical analysis

Statistical analyses will be performed with Stata software (version 13, StataCorp, College Station, USA). Concerning the primary objective, comparison between the randomized groups will be performed using an analysis of covariance with baseline score as a covariate [33]. The correlation between baseline and follow-up scores was also proposed. For other secondary parameters, the comparisons between the randomized groups will be performed using the Student test or the Mann–Whitney test (if the conditions for validity of the Student test are not met, normality will be verified by the Shapiro-Wilk and homoscedasticity by the Fisher-Snedecor test). To study the evolution of the main endpoint (numerical scale pain), data analyses will be performed using mixed models which allow us to consider, on the one hand, time, group and interaction time versus group as fixed effects, and, on the other hand, the within- and between-subject variability in order to visualise the assumption of a difference at 2 months between the two randomized groups that increases up to 3 months and stabilizes at 6 months. Residual normality will be checked for all considered models. When appropriate, anticancer chemotherapy (yes/no) will be studied as a fixed effect in these models before considering subgroup analyses. The comparison between the treatment groups will be performed systematically: (1) without adjustment; and (2) by adjusting other factors whose repartition could be, despite the randomization, unbalanced between the treatment groups. The tests will be two-sided, with a type I error set at α = 0.05. A sensitivity analysis of missing data will be performed to ensure the pertinence of the longitudinal data (MAR (Missing at random) or MCAR (Missing completely at random)). In order to assess the problem caused by missing longitudinal data at 6 months, estimation methods developed by Verbeke and colleagues [34] will be proposed.

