Given that mastectomy with or without chemotherapy can induce NP and cognitive and emotional impairment, these complications represent a real burden for women with breast cancer, and global care is a priority to improve their well-being. If our study confirms preclinical results, memantine given before mastectomy could be a new prophylactic strategy to counteract NP development. It would provide a preventive therapeutic innovation to decrease the incidence of post-operative and chemotherapy-induced NP, cognitive impairment and quality of life impairment and comorbidities that generally accompany breast cancer pathology.

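### The trial is framed as confirming prevention of neuropathic pain and cognitive decline, but it is designed and sized to conclude only on overall pain intensity

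*Protocol article*

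**What the plan says.** The Background paragraph of the abstract sets the aim: to "evaluate if memantine may prevent neuropathic pain development and maintain cognitive function and quality of life in cancer patients". The abstract's Discussion paragraph describes the hypothesis as confirming in women the protective effect seen in animals, and names neuropathic pain and cognitive dysfunction. The main Discussion adds that, if the preclinical results are confirmed, "memantine given before mastectomy could be a new prophylactic strategy to counteract NP development".

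The operative sections are narrower.

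- **Objectives:** the primary question is whether memantine "may prevent pain development at 3 months post-mastectomy when compared to the placebo group". Pain is not qualified as neuropathic.
- **Primary endpoint:** "The primary endpoint is the pain intensity evaluation by numerical scale in memantine and placebo groups at 3 months post-mastectomy".
- **Sample size:** based only on a difference of 1.6 points on that scale, with SD 1.5.
- **Secondary endpoints:** these include "neuropathic pain (Neuropathic Pain in 4 questions, Neuropathic Pain Symptom Inventory), cognition (Trail Making Test, Digit Symbol Substitution Test"), with no order among them.
- **Statistical analysis:** the primary uses analysis of covariance with the baseline score. For the rest, "For other secondary parameters, the comparisons between the randomized groups will be performed using the Student test or the Mann–Whitney test". Also, "The comparison between the treatment groups will be performed systematically: (1) without adjustment; and (2) by adjusting other factors" that turn out unbalanced. Finally, "The tests will be two-sided, with a type I error set at α = 0.05".

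Table 1 shows that DN4, the Trail Making Test and the Digit Symbol Substitution Test are all recorded at screening as well as at each follow-up visit.

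**The concern.** A numerical pain score does not separate neuropathic pain from other post-operative or chemotherapy-related pain. A lower mean score on memantine at 3 months would support less pain. It would not show that neuropathic pain was prevented, still less that cognition was preserved.

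Those two claims would have to come from the secondaries, and the plan for these is weak in three ways.

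- Nothing is sized for them.
- The article describes DN4 as a diagnostic tool with a positive/negative result. Student and Mann-Whitney tests do not suit a binary outcome. The eligibility criteria do not exclude women who already have neuropathic pain, so a plain group comparison at 3 months would mix existing with new cases.
- The cognitive tests have a baseline measurement that the stated secondary comparison does not use, although the primary comparison does use its own.

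At stake is what the final report may say. A positive primary could be read as prevention of neuropathic pain, or an isolated significant cognitive score among many could be read as confirmation of the animal result.

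**Working it through.** **1. The plan's own sample size.** Inputs from the Sample size section: difference 1.6, SD 1.5, two-sided α 0.05, power 0.90.

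n per arm = 2(1.960 + 1.282)² × 1.5² / 1.6² = 2 × 10.51 × 0.879 = 18.5, so 19 by the normal approximation. With the noncentral t distribution, 19 per arm gives 89.2% power and 20 per arm gives 90.8%. The stated 40 women reproduce, for the numerical scale.

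**2. What 20 per arm can show about neuropathic pain.** Input: 23% at 3 months after mastectomy (Discussion). I assume that this rate applies to DN4-positive cases on placebo, that all 20 women per arm are evaluable, and that the treated rates are as listed below. The protocol gives no treated rate.

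- Expected placebo cases: 20 × 0.23 = 4.6.
- Fisher exact, 0/20 against 4/20: p = 2 × C(20,4)/C(40,4) = 2 × 4,845/91,390 = 0.106.
- Fisher exact, 0/20 against 5/20: p = 2 × C(20,5)/C(40,5) = 2 × 15,504/658,008 = 0.047.
- So with no case on memantine, at least 5 placebo cases are needed. P(X ≥ 5) for a binomial(20, 0.23) is 0.50, which is the power for complete prevention.
- Exact power by enumeration: 24% for a fall to 5%, and 9% for halving to 11.5%.
- For 90% power by the normal approximation, halving would need 225 per arm and a fall to 5% would need 76 per arm.

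**3. How many secondary tests.** The article gives no count. This one is rebuilt from the subscales it names and the follow-up visits in Table 1 (day 15, 3 months, 6 months), leaving out the primary test.

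| Instrument | Scores × visits | Tests |
|---|---|---|
| Numerical scale | 1 × 2 | 2 |
| DN4 | 1 × 3 | 3 |
| NPSI | 5 × 3 | 15 |
| BPI | 2 × 2 | 4 |
| McGill | 2 × 2 | 4 |
| Trail Making Test | 2 × 3 | 6 |
| Digit Symbol | 1 × 3 | 3 |
| SF-36 | 9 × 3 | 27 |
| Leeds | 4 × 3 | 12 |
| HAD | 2 × 2 | 4 |
| Total | | 80 |

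With one score per instrument the total is 26. The repeat with adjustment is not counted in either figure.

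Chance of at least one false positive, if every null is true and the tests are independent, is 1 − 0.95^k:

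- k = 26: 74%, with 26 × 0.05 = 1.3 expected.
- k = 80: 98%, with 80 × 0.05 = 4.0 expected.
- Neuropathic and cognitive measures only: k = 12 (four instruments × 3 visits) gives 46%; k = 27 (nine scores × 3 visits) gives 75%.

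Scores from the same woman are likely to be correlated, which lowers these chances. The expected number of false positives does not depend on correlation.

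**The case against.** The strongest reply is that the operative sections agree with one another. Objective, endpoint and sample size all concern pain intensity at 3 months, with one test at its own two-sided 0.05. The wider wording sits in the abstract and the Discussion, where the prophylaxis sentence is conditional, and the main Discussion elsewhere names reducing overall pain and preventing neuropathic pain as two aims. This stands. The mismatch is between framing and design, and the design does not contradict itself.

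A reader might infer that neuropathic pain and cognition are not tested at all, or that the trial lacks error control. Neither is supported: Statistical analysis assigns these measures to a between-group test, and the primary is error-controlled.

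Ranking of secondaries and multiplicity control are commonly left to an analysis plan, which is not shown. Their absence alone is therefore no finding. What remains is what the text does fix: one level of 0.05 for the tests and a stated method for the secondaries, alongside a claim that only these secondaries could support.

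Mann-Whitney does suit the DN4 total out of 10, which the article also describes. The criticism applies only to the positive/negative diagnosis, but prevention of neuropathic pain is a statement about that diagnosis. The adjusted repeat analysis could bring in a baseline score, but only if it happens to be unbalanced.

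Finally, 80 is a reconstruction and 98% an upper-end figure. The text does not say that every subscale is tested at every visit.

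**Conclusion.** The point holds in a limited form. A positive primary would support a conclusion on overall pain intensity at 3 months and no more. As planned, neuropathic and cognitive results can only be exploratory, yet the article presents them as what the trial would confirm.

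For neuropathic pain, power is about 50% for complete prevention and 9% for halving. A non-significant DN4 comparison would therefore be nearly uninformative about a moderate effect. These figures rest on the article's 23%, assumed treated rates and no losses; restricting to women DN4-negative at entry can only reduce the numbers. The documents give no rate of neuropathic pain at entry, so the size of that reduction is unknown.

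For the secondaries together, the chance of at least one false positive is 74% to 98% under independence, depending on the count, and lower with correlation. A reader might go further and call false cognitive or quality-of-life findings near certain. The documents do not support that: the upper figure covers all instruments, including sleep, mood and other pain scales, and assumes independence.

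**What to change.** - State that the primary result supports a conclusion on pain intensity at 3 months only, and that prevention of neuropathic pain will not be claimed from the numerical scale. Bring the aim in the abstract and Discussion into line.
- Report new DN4-positive cases at 3 months (score of 4 or more) among women DN4-negative at D0-15, as a risk difference with an exact confidence interval.
- Analyse the cognitive scores with adjustment for their baseline values, as is already planned for the primary.
- Label these and the other secondaries exploratory, with confidence intervals.

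A fixed testing sequence after the primary is optional. If one is used, the order needs thought: with DN4 ahead of cognition, the cognitive test would be blocked about half the time even under complete prevention, and about nine times in ten under halving.

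The change is one of wording and analysis. DN4 and the cognitive tests are already collected at both time points, and no extra patients, visits or primary alpha are needed. The downside is that fewer outcomes can support formal claims.

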**Methods/Design:**

A randomized clinical trial (NCT01536314) includes 40 women with breast cancer undergoing mastectomy at the Oncology Hospital, Clermont-Ferrand, France. Memantine (5 to 20 mg/day; n = 20) or placebo (n = 20) is administered for 4 weeks starting 2 weeks before surgery. Intensity of pain, cognitive function, quality of life and of sleep, anxiety and depression are evaluated with questionnaires. The primary endpoint is pain intensity on a 0 to 10) numerical scale at 3 months post-mastectomy. Data analysis is performed using mixed models and the tests are two-sided, with a type I error set at α = 0.05.

**Discussion:**

The hypothesis of this translational approach is to confirm in patients the beneficial prophylactic effect of memantine observed in animals. Such a protective action of memantine against neuropathic pain and cognitive dysfunction would greatly improve the quality of life of cancer patients.

**Trial registration:**

ClinicalTrials.gov: NCT01536314 on 16 February 2012

## Background

Medical treatment of neuropathic pain (NP) is still far from being satisfactory, with less than half the patients achieving significant benefit with any pharmacological drug [1]. Several therapies have been developed for the treatment of NP but these methods are not equally effective for all NP patients. N-methyl-D-aspartate receptor (NMDAR) antagonists such as ketamine, memantine or dextromethorphan are potential drugs for NP alleviation [2]. Evidence suggests that NMDAR within the dorsal horn plays an important role in both inflammation and nerve injury-induced central sensitization [3]. Activation of NMDAR is associated with abnormalities in the sensory (peripheral and central) system, resulting in neuronal excitation and abnormal pain manifestations (spontaneous pain, allodynia, hyperalgesia) [4]. Blocking these receptors by antagonists leads to a reduction in pain [5]. A recent review of the literature including 28 randomized clinical trials [2] emphasizes the heterogeneity of doses used, the diversity of pathologies generating neuropathic pain (post-herpetic, post-amputation, diabetes and so forth) and highlights the need to develop clinical trials of good methodological quality with NMDA antagonists. NMDAR antagonists, such as ketamine [6, 7], are prescribed after therapeutic failure with classical treatment but these drugs have severe adverse events that limit their clinical use [8]. Another NMDAR antagonist, memantine, prescribed in Alzheimer’s disease to maintain cognitive function, has minimal side-effects at doses within the therapeutic range, probably because of its specific mechanism of action as it is an uncompetitive antagonist with moderate affinity, strong voltage-dependency and rapid unblocking kinetics [9–11]. Concerning NP alleviation, memantine shows controversial results in human studies [6, 12–15]. We recently demonstrated for the first time in an animal surgical NP model, that memantine prevents the development of NP symptoms and the impairment of spatial memory [16]. With a translational approach, we present a clinical study where memantine (versus placebo) is administered 2 weeks before and 2 weeks after mastectomy in 40 women suffering from breast cancer. Confirmation of preclinical results in this clinical study would constitute a major step for NP prevention by memantine and maintenance of cognition and quality of life in these vulnerable patients.

## Methods/Design

We are conducting a randomized, placebo-controlled clinical trial in the Oncology Hospital, Clermont-Ferrand, France, in 40 women undergoing total mastectomy for breast cancer. The study has been approved in December 2011 by the regional Ethics committee (CPP Sud-Est, France, number AU917) and registered on 16 February 2012 at “http://www.clinicaltrials.gov” (NCT01536314). Women provide written informed consent prior to their participation in the study during their anesthesiology visit. After baseline assessments (day (D)_−15_) of pain intensity, cognition, quality of life and quality of sleep questionnaires, participants are randomized into two parallel groups: memantine (n = 20) or placebo (n = 20). Memantine or placebo (lactose) is given orally for 4 weeks starting 2 weeks before surgery. Memantine is given in increasing doses: 5 mg/day for 3 days; 10 mg/day for 3 days; 15 mg/day for 3 days and 20 mg/day for 5 days. Endpoints are reassessed 15 days (D_0+15_), 3 months (D_0_ + 3 months) and 6 months (D_0_ + 6 months) post-mastectomy. In order to maintain a good compliance and to verify that women do not develop adverse events, patients are called once a week by phone. A booklet for monitoring is completed daily by the patient for 6 months from the day of surgery. Detailed information on the present study is summarized in Figure 1.

**Figure 1 Fig1:**
[figure not shown]
**Study design.**

### Eligibility

#### Inclusion criteria

Women are eligible for this study if they are at least 18 years old, with a diagnosis of breast cancer, programmed for mastectomy with or without axillary dissection, able to understand and willing to follow the study protocol.

### Exclusion criteria

Exclusion criteria comprise contraindications for memantine and hypertension, severe cardiac insufficiency or diabetes (Type I and II), alcohol addiction and treatment with specific drugs (amantadine, ketamine, dextromethorphan, L-Dopa, dopaminergic, anticholinergic agonists, barbituric, neuroleptic, IMAO, antispastic agents, dantrolen or baclofen, phenytoin, cimetidine, ranitidine, procainamide, quinidine, quinine, nicotine, hydrochlorothiazide, warfarin). Childbearing age, no use of effective contraceptive method, pregnancy or lactation, involvement in another clinical trial and inability to comply with the requirements of protocol are other exclusion criteria.

### Objectives

The primary objective of this study is to evaluate if memantine administered before and after mastectomy may prevent pain development at 3 months post-mastectomy when compared to the placebo group. The endpoint at 3 months was chosen because chronic pain is usually defined as pain lasting longer than 2 to 3 months [17, 18], and 6 months was included as a secondary endpoint.

The secondary objectives are to estimate at 3 and 6 months post-mastectomy the pain intensity, the analgesic concomitant medications, the impact of treatment (memantine/placebo) on cognitive function, quality of life, sleep, anxiety and depression, the impact of cancer chemotherapy-induced pain and cognitive impairment and the prevalence of phantom breast experience.

### Definition of endpoints and outcome measures

#### Primary endpoint

The primary endpoint is the pain intensity evaluation by numerical scale in memantine and placebo groups at 3 months post-mastectomy. The scale ranges from 0 (no pain) to 10 (maximal tolerable pain).

#### Secondary endpoints

Secondary endpoints are the evaluation of pain at the screening visit, at 2 weeks, 3 months and 6 months after mastectomy (numerical scale, Brief pain Inventory, McGill pain questionnaire), neuropathic pain (Neuropathic Pain in 4 questions, Neuropathic Pain Symptom Inventory), cognition (Trail Making Test, Digit Symbol Substitution Test), sleep (Leeds sleep questionnaire), quality of life (Short-Form-36), and anxiety and depression (Hospital Anxiety and Depression scale). The summary of the different evaluations for a patient is reported in Table 1.

**Table 1 Tab1:** **Summary of evaluation for a patient**

Visit	Screening/informed consent	Surgery (mastectomy)	Hospital stay	Follow-up	Follow-up	Follow-up
Day of visit	D_0-15_	D_0_	D_0_ to D_0 + 15_	D_0 + 15_	D_0 + 3_ months	D_0 + 6_ months
Filling of questionnaires						
**1- Pain**						
Numerical Scale	+	-	+	+	+	+
DN4	+	-	-	+	+	+
NPSI	-	-	-	+	+	+
BPI	-	-	-	-	+	+
McGill pain questionnaire	-	-	-	-	+	+
**2- Cognition**						
Trail Making Test	+	-	-	+	+	+
Digit Symbol Substitution Test	+	-	-	+	+	+
**3- Quality of life**						
SF-36	+	-	-	+	+	+
**4- Sleep**						
Leeds questionnaire	+	-	-	+	+	+
**5- Anxiety/Depression**						
HAD scale	+	-	-	-	+	+
**6- Concomitant medication recording**						
Treatments (analgesics, antidepressants, etc.)	+	+	+	+	+	+

+, Questionnaire performed; -, questionnaire not carried out; BPI, Brief Pain Inventory; DN4, Neuropathic Pain in 4 questions; HAD scale, Hospital Anxiety and Depression Scale; NPSI, Neuropathic Pain Symptom Inventory; SF-36, Short-Form-36.

##### Brief Pain Inventory

This self-administered questionnaire provides information on the intensity of pain, along with the degree to which the pain interferes with the everyday functioning of life including: mood, walking, general activity, relations with others, sleep, enjoyment of life [19].

##### McGill pain questionnaire

This questionnaire allows the patient to describe pain experienced during the last 48 hours [20]. It has fifty eight qualifiers divided into sixteen items (A to P). Each qualifier is rated from 0 to 4, where 0 = absent, 1 = low, 2 = moderate, 3 = strong, 4 = very strong. The score is divided between two subclasses: sensory subclass (items A to I) and emotional subclass (items J to P).

##### Neuropathic pain: “Neuropathic Pain in 4 questions”

Neuropathic pain in four questions is a clinical tool for the diagnosis of neuropathic pain [21]. This questionnaire has four questions divided into 10 items related to the interview (that is, symptoms) and to the sensory examination (that is, signs). The investigator asks and examines the patient and notes a response “no” or “yes” for each item: “yes” is scored as “1” and “no” is scored as “0”. The sum of scores gives the total score of the patient (out of 10). Neuropathic pain in four questions is considered as positive if the patient obtains a score of 4/10.

